### Outcomes and measures

#### Primary outcomes

The three primary outcomes each address one of the three central aims of the trial: (i) the difference in trajectory of change of clinical severity between groups, using the parent-rated Brief Problem Monitor [42]; (ii) clinicians’ use of evidence-based content during therapy sessions (based on audio-recorded therapy sessions); (iii) total time spent by clinicians delivering therapy (using therapy logs).

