#### Weekly measurements

The allocated research assistant completes the weekly telephone assessments with the parent and the youth participant for the duration of treatment. The weekly assessment is designed not to exceed 10 minutes, to minimize participant burden.

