### Sample size

Overall, a sample size of 60 clinicians and 400 patients will provide sufficient power to detect effect sizes of approximately 0.37, well below the effect size shown by the comparable USA study [30]. The initial power calculation was to allow independent analysis to be undertaken for Māori and Pacific participants and ensured sufficient power (80 %) to detect moderate effect sizes of between 0.61 and 0.70 as statistically significant (two-tailed *α* = 0.05) in these groups (equivalent to the effect sizes found in the USA study [30]). This estimate allowed for a 15 % attrition rate in clinicians and in clients (based on the 12.3 % attrition rate reported in Weisz *et al.* [30] and adjustment for the clustering of patients with clinicians (intraclass coefficient = 0.1)). We assumed approximately six to eight patients per clinician (approximately 400 patients). If fewer clinicians were available within the targeted services, we planned to increase the number of participants per clinician to ensure that we maintained statistical power. The intention was to recruit approximately 12 clinicians working in Kaupapa Māori services and approximately 12 clinicians working in Pacific services. While this seemed feasible in the planning stages, when we were actually conducting the trial, there were a number of staffing difficulties in the services overall, and these impacted more particularly in the Kaupapa Māori and Pacific services, perhaps because of the smaller pool of people in the workforce. This led to difficulty in recruiting clinicians working in Māori and Pacific services, with resulting reduced ability to recruit participants to the trial from those services. It became evident that we would not reach the targets for Māori and Pacific participants to allow ethnic-specific analysis, as planned. An interim blinded-to-treatment allocation, single group, power analysis was undertaken (when approximately 50 participants had completed treatment) to determine the total number of participants needed to show overall clinical effectiveness for the whole sample. This summary produced a standard deviation for the change in the parent-rated Brief Problem Monitor of 4.4, which indicated that to show a clinically important difference in the change (>2 units) as statistically significant (two-tailed *α* = 0.05) with 80 % power, a total sample size of 160 participants would need to be recruited. A total sample of 200 participants would provide 90 % power for this comparison. Although a reduced final sample size would compromise the ethnic-specific analysis, it was felt that the primary question of whether MATCH-ADTC improved the trajectory of change of clinical severity more than usual care could be conclusively addressed with 200 participants. Based on the ongoing recruitment, it was anticipated that this total recruitment could be achieved if we extended the timeline and recruited until the end of June 2015.

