#### Overall analysis

The comparability of the baseline status of both treatment groups (i.e., MATCH-ADTC and usual care) will be determined using descriptive analysis, in terms of age, sex, clinical symptom severity, diagnosis, and ethnicity. The two randomized treatments may vary in duration, so that post-intervention and follow-up (three months after treatment has ended) analyses are potentially confounded by treatment duration. To allow an unconfounded interpretation, we propose to use the trajectories of change across time on the parent-rated Brief Problem Monitor as our primary outcome measure. The trajectory of change was selected in part because the duration of treatment and number of sessions provided to individual youth are variable in usual clinical services, and also within the structure of the MATCH-ADTC program, such that the usual care and MATCH-ADTC groups could not be matched for duration or number of sessions. In addition, we want to compare the results of the current study with that of a trial from the USA that used this method [30]. The primary analysis will be based on the intention-to-treat population, but sensitivity analysis will be undertaken on the per-protocol population.

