#### Primary outcomes

##### Clinical outcomes

The difference in the trajectories between groups will be tested using a mixed effects regression model: *a*_0_ (intercept) + *a*_1_ (participant) + *a*_2_ (treatment group) + *a*_3_ (time) + *a*_4_ (treatment × time) and intercept and participant as random effects. These analyses will further include terms for:Service type (i.e., Kaupapa Māori, Pacific and ‘mainstream’ CAMHS);Clinicians’ previous training in evidence-based therapy;Baseline symptom level; andMedication use.

Although we are now unable to conduct ethnic-specific analysis, summary data will be used to illustrate whether there is a broad consistency of the clinical outcome results across ethnicity groups.

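### The primary trajectory model has no random slope for time, so its treatment × time test is anti-conservative if youths differ in rate of change; by how much cannot be fixed from the protocol

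*Protocol article*

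**What the plan says.** Under Primary outcomes, the clinical outcome is "the difference in trajectory of change of clinical severity between groups, using the parent-rated Brief Problem Monitor". Overall analysis gives the reason for this choice: treatment length may differ between arms, so post-treatment comparisons could be confounded by duration.

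Under Clinical outcomes, "The difference in the trajectories between groups will be tested using a mixed effects regression model". The model is then listed term by term: intercept, participant, treatment group, time and treatment × time, "and intercept and participant as random effects". Four covariates follow (service type, clinician's earlier training, baseline symptom level, medication use). None of them lets the rate of change vary from youth to youth. The article states no residual correlation structure and no robust standard error.

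Under Weekly measurements, the research assistant "completes the weekly telephone assessments with the parent and the youth participant for the duration of treatment". Overall analysis adds that "the duration of treatment and number of sessions provided to individual youth are variable in usual clinical services".

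Under Sample size, "This summary produced a standard deviation for the change in the parent-rated Brief Problem Monitor of 4.4", and the revised target is set to detect "a clinically important difference in the change (>2 units) as statistically significant (two-tailed" α = 0.05), with 160 youths for 80 % power and 200 for 90 %.

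**The concern.** Youths are randomized individually and the outcome is a slope. The treatment × time contrast is therefore a comparison of mean slopes between two groups of youths, and its standard error must reflect how much slopes differ from youth to youth. A random intercept absorbs differences in level only. Any spread in slopes falls into the residual, where it is averaged over all weekly scores as if it were independent week-to-week noise. Adding weekly scores shrinks that noise, but it does not shrink the true spread of slopes.

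The consequence is a confidence interval that is too narrow and a p-value that is too small for the clinical primary hypothesis. The two sections of the article also use different error terms: Sample size uses the between-youth spread in change, while the analysis model largely omits it.

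**Working it through.** **1. The article's own figures.** Inputs from Sample size: SD of change 4.4, difference 2, two-sided α 0.05; 1:1 allocation from Design. SE = 4.4 × √(4/N), and power = Φ(2/SE − 1.96).

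- N = 200: SE = 0.622, 2/SE = 3.214, power 89.5 % (stated 90 %).
- N = 160: SE = 0.696, 2/SE = 2.875, power 82.0 % (stated 80 %).

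The figures reproduce. They show that the trial was sized on between-youth variation in change.

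**2. Error term of the model as written.** Let m be the number of equally spaced weekly scores per youth, T = m − 1, Sxx = m(m² − 1)/12, vb the variance of true slopes and ve the residual variance. For equal lengths and independent residuals:

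- the true variance of one youth's fitted slope is vb + ve/Sxx;
- the variance that the random-intercept model uses is about ve/Sxx + vb/(m − 1).

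Only a fraction 1/(m − 1) of the slope variance reaches the test. With VR the ratio of the first to the second, actual α = 2 × [1 − Φ(1.96/√VR)].

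**3. Tie to the stated SD (assumption).** 4.4² = vb × T² + 2 × ve. Let f be the share of 4.4² that is true slope variation. Neither f nor m is in the article, so both are varied.

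**4. One case in full.** Assume T = 20 weeks (m = 21) and residual SD 2.5.

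- vb = (19.36 − 12.5)/400 = 0.01715, so f = 6.86/19.36 = 35 %.
- Sxx = 21 × 440/12 = 770, and ve/Sxx = 6.25/770 = 0.00812.
- True variance: 0.01715 + 0.00812 = 0.02527.
- Variance used: 0.00812 + 0.01715/20 = 0.00897.
- VR = 2.82, 1.96/√2.82 = 1.17, actual α about 0.24.

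With 100 per arm, the SE of the arm difference in change at week 20 is 20 × √(0.00897 × 2/100) = 0.27 as written and 20 × √(0.02527 × 2/100) = 0.45 with slope variance included. The sample-size calculation used 0.62.

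**5. Range.** Simulated type I error with 200 youths, 1:1, no treatment effect and 2000 runs per cell. The random-intercept test was computed by the within-person estimator, which gives the same slopes as the random-intercept fit when lengths are equal. Columns are 9 / 17 / 27 weekly scores. In the last column these are mean lengths, drawn from a Poisson distribution limited to 4–60.

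| Slope share f | Equal lengths | Varying lengths |
|---|---|---|
| 0 % | 0.05 / 0.04 / 0.05 | 0.05 / 0.05 / 0.05 |
| 10 % | 0.07 / 0.10 / 0.11 | 0.11 / 0.12 / 0.14 |
| 25 % | 0.10 / 0.15 / 0.20 | 0.20 / 0.22 / 0.26 |
| 50 % | 0.22 / 0.29 / 0.38 | 0.36 / 0.40 / 0.46 |
| 75 % | 0.30 / 0.46 / 0.54 | 0.49 / 0.53 / 0.62 |

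The closed form in step 2 agrees with the equal-length column to within about 2.5 percentage points (for example 0.07 / 0.09 / 0.11 at 10 % and 0.20 / 0.29 / 0.38 at 50 %). When the slope variance enters the error term (generalized least squares with known variance components), simulated type I error is 0.04–0.06 in every cell.

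**6. Residual structure.** The table assumes independent residuals. A large-sample calculation over 12 to 26 weeks and residual SDs of 2.0 to 2.9, with an assumed between-youth intercept SD of 5, gives 9–43 % with independent residuals, 8–34 % with a first-order autoregressive residual, and 5.4–12.5 % with an autoregressive part plus independent error.

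**The case against.** Four objections carry weight.

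*The wording is loose.* Naming both the intercept and the participant as random is redundant if a single participant-level intercept is meant, so the sentence may be a garbled version of a fuller model. That is possible, but no reading of it makes time random. If a slope was intended, the sentence needs correcting anyway.

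*An article condenses the plan.* This stands for the residual covariance and the standard-error method. Their absence is no fault, and independence cannot be read into silence. It does not stand for the random effects, which the article states.

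*The size is assumed.* This stands. The slope share and the number of weekly scores are not given. Nor is the interval over which the SD of 4.4 was measured; it came from a blinded summary when about 50 youths had completed treatment. Splitting it into linear slope and weekly noise is a modelling assumption. The heterogeneity that the Discussion mentions concerns clinical presentation, not rates of change.

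*Comparability with the USA trial.* Overall analysis says trajectories were chosen partly to match that trial's method. Its random effects are not shown here, and precedent would not make the standard error valid. It is still a fair reason to report a matching analysis as well.

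A reader might infer that type I error is certainly inflated several-fold, or that a true null would be rejected in at least a fifth of trials. The documents do not support either as an unconditional statement: at a 10 % slope share with 9 equal-length scores the rate is about 7 %, or 1.4 times nominal.

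**Conclusion.** The point holds as a fault in the stated model. For a rate-of-change outcome, the listed random effects omit the variance component against which treatment × time should be tested. The direction is clear: the test is anti-conservative whenever slopes differ between youths, and nominal only if all youths in an arm share one slope.

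The size is conditional. Under independent residuals, equal lengths and the split of 4.4 used above, actual α is about 1.4 to 2.2 times nominal at a 10 % slope share, 2 to 4 times at 25 %, and 4 to 8 times at 50 %. Varying treatment lengths, which the article expects, raise these figures. A serial-correlation term in the fitted model would lower them, in the most favourable form to near nominal.

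The sample-size figures themselves are not in error. Clustering of youths by clinician is a separate matter and plays no part in this conclusion.

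**What to change.** State the primary model with a participant-level random intercept and a participant-level random slope for time, with unstructured covariance between them. Say that treatment × time is tested against between-youth slope variance. If comparability with the USA trial is wanted, report the random-intercept model as a sensitivity analysis.

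The cost is one line in the model specification and wider, correct confidence intervals. No new data are needed. The article reports that recruitment is still under way, so the line can be settled before any comparison by arm.

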## Methods

### Design

This study is a multi-site effectiveness randomized controlled trial comparing MATCH-ADTC with usual care [41]. Prior to randomization, written informed consent is obtained from each participant. Randomization is implemented on two levels: first, randomization of participating clinicians, then randomization of youth participants. For the randomization of clinicians, all clinicians from participating services were invited to participate and provide written informed consent. Consenting clinicians were block randomized (by service or team) in a 1:1 ratio to MATCH-ADTC or usual care. The block size varied across sites, depending on the number of individual clinicians recruited from each site. Clinicians were stratified on the basis of previous training in evidence-based therapies (i.e., those with versus those without training in cognitive behavioral therapy or behavioral parent training). Clinicians randomized to MATCH-ADTC received training in MATCH-ADTC at the beginning of the study prior to the recruitment of youth participants. Those randomized to usual care will receive training at the end of the study (once all follow-up data have been collected). Randomization of youth participants occurs after a clinician-administered eligibility check and once written consent has been obtained. Youth participants are then randomized in a 1:1 ratio to receive MATCH-ADTC or usual care, with participants stratified by sex and ethnicity (Māori, Pacific, or ‘other’). Web-based randomization procedures are used to determine treatment allocation. Data from all participants will be included in data analysis, irrespective of whether or not all assessments have been completed.

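### The primary trajectory model leaves out sex and ethnicity, the factors on which youths are randomised, and gives no covariate a time interaction, without which it can barely adjust the treatment × time test

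*Protocol article*

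**What the plan says.** The Design section allocates youths 1:1, "with participants stratified by sex and ethnicity" in three levels (Māori, Pacific, other). Clinicians are randomised separately: "Consenting clinicians were block randomized (by service or team) in a 1:1 ratio", and "Clinicians were stratified on the basis of previous training in evidence-based therapies".

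The Clinical outcomes section writes the primary model as intercept, participant, treatment group, time and their product ("treatment × time) and intercept and participant as random effects"). It continues "These analyses will further include terms for" four items: service type (Kaupapa Māori, Pacific, mainstream), clinicians' previous training, and finally "Baseline symptom level; andMedication use".

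Sex otherwise appears in the analysis only in the descriptive baseline comparison (Overall analysis). Ethnicity appears there and in descriptive summaries of outcome consistency (Clinical outcomes). Table 1 shows the Brief Problem Monitor collected at baseline, weekly during therapy, after intervention and at three months.

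**The concern.** An analysis should normally contain the factors used to stratify the randomisation. Stratifying balances the arms on those factors. If the factors predict outcome and the model ignores them, the model-based standard error tends to be too large, and the precision gained by stratifying is not used. Here the covariate list is written out. It includes the clinicians' stratification factor but not the two youth factors, although youths are the unit of the clinical comparison. Service type does not stand in for ethnicity: it describes the clinic, and a Māori or Pacific youth may attend a mainstream service.

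The second half concerns how covariates act on a slope test. A time-constant main effect moves a youth's whole curve up or down and leaves its slope alone. If the four listed terms enter only in that way, baseline symptom level is nominally adjusted for but does almost nothing for the primary contrast. Sex and ethnicity added in the same way would do no more.

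**Working it through.** **1. Lists side by side**

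| Factor | Used in randomisation (Design) | In primary model (Clinical outcomes) |
|---|---|---|
| Youth sex | yes | no |
| Youth ethnicity (3 levels) | yes | no |
| Clinician previous training | yes (clinicians) | yes |
| Service or team | block for clinicians | only as service type |
| Baseline symptom level | no | yes |
| Medication use | no | yes |

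**2. Why a level term does not touch the slope contrast**

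With the same visit times for everyone, the treatment × time estimate is the difference between arms in the mean of the per-youth slopes, where slope_i = Σ(t − t̄)·y_it / Σ(t − t̄)². Adding a constant c_i to all of a youth's scores adds c_i·Σ(t − t̄) = 0 to the numerator. The slope, and so the contrast, is unchanged.

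**3. Does it still hold with unequal follow-up?**

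The Overall analysis section says duration varies between youths, so this was simulated. All parameters are assumed: 200 youths; 16 weekly scores each, or 4 to 29; random-intercept SD 2, random-slope SD 0.08, residual SD 2.5; slopes related to sex and to one standardised baseline covariate (0.08 each); 150 replicates; variance components treated as known. The SD of the treatment × time estimate was:

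| Visits | Random effects fitted | No covariates | Level terms | Covariate × time |
|---|---|---|---|---|
| 16 each | intercept | 0.0258 | 0.0258 | 0.0227 |
| 16 each | intercept and slope | 0.0270 | 0.0270 | 0.0234 |
| 4–29 | intercept | 0.0301 | 0.0293 | 0.0230 |
| 4–29 | intercept and slope | 0.0253 | 0.0252 | 0.0204 |

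With equal visits, the estimates with and without level terms agree to about 1e-15. With unequal visits they differ on average by 0.0018 (random intercept only) or 0.0009 (with random slope).

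The gain in the last column depends on the assumed associations, which are strong. The covariates carry 0.08² + 0.08² × 0.25 = 0.0080 of slope variance against 0.08² = 0.0064 left over, that is 0.0080 / 0.0144 = 56 %. The table shows which terms act on the contrast, not how much this trial would gain.

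**4. Baseline score as outcome row or covariate**

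A second simulation under assumed parameters (200 youths, 17 scores, random intercept and slope, 1,000 replicates) gave these mean standard errors for treatment × time:

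- unadjusted: 0.0290
- sex × time only, baseline score kept as outcome row: 0.0289
- baseline × time and sex × time, baseline score also kept as outcome row: 0.0268
- the same covariates, post-baseline scores only: 0.0291

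The last two are different models; their estimates differed by 0.0056 on average. In this set-up the gain appeared only when the baseline score was used twice.

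**5. Link to the sample size**

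Inputs from the Sample size section: SD of change 4.4, difference 2, two-sided α 0.05.

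- N for 90 %: 2 × [2 × (1.960 + 1.282)² × 4.4² / 2²] = 203.4, so 204. The plan says 200.
- Power at 200: 2 / (4.4 × √(2/100)) = 3.214; 3.214 − 1.960 = 1.254; Φ = 89.5 %.
- N for 80 %: 152. Power at the stated 160 is 82.0 %.

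The plan's figures are reproduced closely, and neither uses covariates. If covariates explain a share R² of the variance in change, the SD becomes 4.4 × √(1 − R²):

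| Assumed R² | SD | Power at 200 | N for 90 % |
|---|---|---|---|
| 0 | 4.40 | 89.5 % | 204 |
| 0.05 | 4.29 | 90.9 % | 194 |
| 0.10 | 4.17 | 92.3 % | 184 |
| 0.20 | 3.94 | 94.9 % | 164 |

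The documents give no R². The calculation is for a change score, so carrying it over to a slope test is approximate.

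**The case against.** The strongest reply is that the article nowhere says the covariates are main effects only. It says terms will be included, and a fuller analysis plan, not shown, may specify time interactions. That stands: main effects are the plain reading because treatment × time is the only interaction written, but a reader should not take it as stated. The omission of sex and ethnicity is different, because the covariate list itself is on the page.

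A second reply is that, by the argument above, adding sex and ethnicity as main effects would hardly change the test, so their omission does no harm. This too is largely right, and it is why the point needs both parts: the strata should be in the model, and in a form that acts on the slope.

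Third, exact invariance needs equal visits and time-constant covariates. Follow-up here varies, and Table 1 records medication use at three times, so it could enter as time-varying. The simulation shows that the effect of unequal visits is small, not zero.

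Four stronger readings are tempting and not supported:

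- *That the treatment comparison is biased or type I error inflated.* Randomisation protects the comparison, chance imbalance is covered by the standard error, and ignoring strata tends to make the test conservative.
- *That a definite share of precision is lost.* Every simulated gain rests on assumed associations. The gain from sex alone was about nil, and the gain from baseline vanished once that score was used only as a covariate.
- *That baseline severity is the main predictor of rate of change here.* The documents give no evidence on this.
- *That individual service must be added.* It was a block for clinicians, not a youth stratifier, and as a main effect it would do nothing for the slope test.

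Finally, the change is not wholly free. Māori and Pacific recruitment fell short, so ethnicity cells may be sparse, and ethnicity overlaps service type.

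**Conclusion.** The point holds in this form. The primary model omits the two factors on which youths are randomised while including the clinicians' factor. As plainly read, its covariates adjust treatment × time not at all with equal visits and negligibly with the follow-up expected here. The consequence is modest: no bias, no error in the stated sample size, and a standard error that may be somewhat too large. The gain in power at 200 participants lies between nothing and about 5 percentage points (89.5 % to 94.9 %) if covariates explain an assumed 0 to 20 % of the variance in change. The lower end is a real possibility. The case for the change rests mainly on making the analysis agree with the randomisation, and on fixing the form of the covariates before unblinded data are seen.

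**What to change.** Before unblinded analysis:

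- Add sex and three-level ethnicity to the primary model. Enter sex, ethnicity and baseline symptom level together with their interactions with time, and keep treatment × time as the test.
- State for service type, previous training and medication use whether a time interaction is included.
- Pre-specify a rule for pooling ethnicity levels if cells are sparse or overlap heavily with service type.
- State whether the baseline Brief Problem Monitor score is an outcome row or a covariate, not both. If it is the covariate, the outcome rows are post-baseline scores and baseline × time is in the model. If it is an outcome row, that score leaves the covariate list together with its time interaction. These are different models, so the choice must be made in advance.

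The cost is wording and a few degrees of freedom: 1 + 2 for the added main effects of sex and ethnicity, and 1 + 2 + 1 for the time interactions of sex, ethnicity and baseline, seven parameters in all. The variables are already collected, and the Trial status section shows recruitment still open.
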